## Methods

### Study design

The PREVED study is an ongoing open-label, monocentric, randomized (1:1:1) controlled superiority trial, parallel-designed, three-armed with:
A control group: group (1)An intervention group in neutral location: group (2)An intervention group in contextualized location: group (3)

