Furthermore, the study was preceded by the creation of a “DisProSE Group” steering committee, a consortium of researchers, local actors, and decision-makers who co-built the intervention, initially developed by a mutual insurance company, according to PREVED’s aims and to behavior change techniques (BCT) taxonomy [46].

After complete recruitment, we could analyze the intervention, which involved 12 of the 16 BCTs, in view of diversifying approaches (Table 2).

**Table 2 Tab2:** Behavior change techniques (BCT) used for the intervention of PREVED study

Grouping of BCT taxonomy	Chosen BCT in each BCT group	Example of an intervention
*Goals and planning*	Problem solving	- To identify behaviours that are easy to implement daily to reduce exposure to endocrine disruptors chemicals (EDC) (example: replace plastic with glass)
	Action planning	- To integrate the purchase of primary products into your personal planning and devote time to manufacturing cosmetics at home
*Feedback and monitoring*	Not applicable	- No feedback between the workshops/Only a series of workshops by participant
*Social support*	Not applicable	- Few attendants came to the workshops
*Shaping knowledge*	Training on how to perform the behavior	- To learn to read package labels - To learn to prepare cookies and cosmetics at home
	Behavioral experiments	- To appreciate the changes implemented daily to reduce their exposure to EDCs thanks to the three-time questionnaire which to compare her consumption before and after
*Natural consequences*	Information about health consequences	- To respond to participants' questions about the known effects of EDCs exposure during pregnancy
	Information about social and environmental consequences	- To present the consequences of behaviours aimed at reducing EDCs exposure on the environment (example: waste reduction through homemade products)
*Comparison of behavior*	Demonstration of the behavior	- To teach how to make one’s own cosmetics
*Associations*	Prompts/clues	- To highlight leaflets and documentation at home
*Repetition and substitution*	Behavioral practice/rehearsal	- To integrate the manufacture of cosmetics into your schedule: the recipes offered were inexpensive and easy to integrate into a routine without constraints
	Behavior substitution	- To avoid heating food in plastic dishes with a microwave oven
	Habit formation	- To encourage participants to ventilate the house for 20 minutes/day

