No concomitant intervention is prohibited. Women randomized in the control group are told that they are entitled to have the program after the end of the study (1 year after delivery).

The list of pregnant women is obtained through pregnancy declarations, which are centralized in rance by “*Protection Maternelle et Infantile*” (maternal and child protection) or PMI. The investigator sends to eligible women an informative postal mail with a prepaid envelope. Women who wished to participate in PREVED study confirmed their interest by phone or mail.

To improve enrolment, information leaflets are sent to general practitioners and midwives working in the enrolment area. To achieve representative and adequate enrolment, PMI’s midwives were trained to present the PREVED study to pregnant women. Local actors in social centers and the associative sector also assisted in enrolment. The first participant was enrolled on 17 April 2017.

The intervention consisted of a sequence of three workshops held between the second and the third trimesters of pregnancy. It incorporated the results of a previous workshop [43] and aimed to identify pollutant sources in daily life and to offer accessible and pragmatic alternative solutions by promoting the sharing of know-how and experience in a positive and non-alarmist approach. Three themes are addressed (Table 3). Any participant may at any time withdraw from this study and adherence participation is encouraged with adapted meeting.

**Table 3 Tab3:** Detailed workshops for the intervention of PREVED study

	Workshop 1	Workshop 2	Workshop 3
***Theme***	Indoor air quality	Nutrition	Personal care products
***Duration***	2 h	2 h	2 h
***Participants***	10 people: pregnant women ± spouse, friend, or parent	10 people: pregnant women ± spouse, friend, or parent	10 people: pregnant women ± spouse, friend, or parent
***Facilitator***	Medical advisor for indoor environments	Dietician trained in environmental health	Cosmetologist
***Pedagogic objectives***	- To detect and reduce sources of domestic air pollution - To share know-how, experiences, and information on alternatives	- To identify food pollutants - To share know-how, experiences, and information on alternatives	- To identify necessary elements to make healthy choices of personal care products and clothes - To share know-how, experiences, and information on alternatives

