The DisProSE group produced an information leaflet providing advice on ways of reducing EDC exposure in relation to the aforementioned themes. This leaflet was designed according to the principles of health literacy to be as accessible and comprehensible as possible [47]. All participants, including group 1, receive it during the first home visit. The only difference between group 2’s workshops and group 3’s workshops is the location of the intervention.

Fig 1. summarizes the conduct of PREVED study.

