Baseline measurements of the three trial arms will be compared using paired *t* tests and *χ*^2^ tests for the analysis of Q1 and EDC concentrations. The results of Q2 in the three groups will be compared by dimension using ANOVA analyses. An intention-to-treat analysis will carried out, and then a per-protocol analysis in aim to take into account population relating to protocol non-adherence.

Main outcome will be compared between home visit 1 and home visit 2. The rest of analysis will be performed between home visit 1, home visit 2, and home visit 3. Multivariate logistic regression will be performed to assess factors influencing main and secondary outcomes.

All statistical analyses will be performed using SAS 9.4® (SAS Institute, Cary, North Carolina, USA).

No interim analyses are scheduled.

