Furthermore, the main feature of PREVED study is to consider all aspects of lifestyle and to underscore key functions such as sharing of know-how, sharing of experiences and information between participants. In fact, few environmental promotion interventions have shown that EDC exposure was reduced by changing lifestyle. However, previous studies assessed the impact by taking into account only one component of lifestyle, such as nutrition or cosmetics [67, 68] and did not include the dimension of “know-how” [69]. Moreover, these studies took EDC concentrations in urine as their main outcome, even though analysis of the latter may be unreliable [70–72] and did not provide information about psychosocial aspects. This facet will be explored by the psychosocial questionnaire Q2 in our study. Concerning assessment of exposure to EDCs, we chose urine matrix samples because spot samples of urines are not restrictive and ensure optimal acceptability for the pregnant women participating. Twenty-four-hour urine collection may have been preferable, due to non-influence of the time of day. However, spot samples of urines provide reasonably reliable information on impregnation by BPA and PB during pregnancy [73–76].

We made sustained efforts to minimize information bias. Notwithstanding the absence of blindness, the investigator’s practices and behaviors are likely to vary during visits, according to allocation group. That is why hetero administration of questionnaires by a single trained assessor, with a standardized interviewer’s guide, has been adopted. Furthermore, selection bias is controlled by trained PMI nurses wishing to facilitate the enrolment of pregnant women facing difficulties. Enrolment bias is thereby avoided, whereas preceding studies highlighted the fact that participants for this type of study are mostly women with a high socio-economic level [48]. However, in such a cohort, selection bias can still be expected [77] especially for pregnancy cohorts, insofar as women with a high socio-educational level are likely to feel more concerned [78, 79]. We will probably need to determine how to reach populations more effectively in precarious situations. At the time of the analysis, results will be adjusted on confounding factors that affect the psycho-social dimensions and have been highlighted in this study.

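### The planned per-protocol analysis of non-adherence is not a randomised comparison, because workshops can be missed only in groups 2 and 3; a complier-average estimate should be added and per-protocol labelled descriptive

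*Protocol article*

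**What the plan says.** The protocol article, under Data collection, management, and analysis, plans an intention-to-treat analysis first, "then a per-protocol analysis in aim to take into account population relating to protocol non-adherence". It names no other method for non-adherence and does not say who belongs to the per-protocol set. The main outcome is to be compared between home visit 1 and home visit 2.

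The design is described under Study design as a "randomized (1:1:1) controlled superiority trial" with three arms. Under Participants and interventions:

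- For groups 2 and 3, "The intervention consisted of a sequence of three workshops held between the second and the third trimesters of pregnancy".
- The control group has only the leaflet, and of the leaflet the article says: "All participants, including group 1, receive it during the first home visit".
- Controls are told that "they are entitled to have the program after the end of the study (1 year after delivery".
- In Table 2, the social support row carries the remark "Few attendants came to the workshops".

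The Discussion adds, about pregnancy cohorts, that "women with a high socio-educational level are likely to feel more concerned".

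**The concern.** A control woman has no workshop to miss and no access to one during follow-up. Any exclusion based on workshop attendance, whether the threshold is one, two or three sessions, therefore removes women from groups 2 and 3 only. The control women who would also have stayed away cannot be identified, so they remain in the comparison. What is left sets women who chose to come against a control group containing both kinds of women.

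If the choice to attend goes with lower consumption of industrial food, or with a readiness to cut it down whatever the arm, the per-protocol difference mixes the workshop effect with who attended. It can then show a difference where the workshops did nothing. This would matter most if attendance turned out low, because intention to treat would be diluted and readers would be drawn to the per-protocol figure.

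**Working it through.** **Inputs from the article (Sample size).** Control rate 83%; hypothesised rate 60%; two-sided 5% level; 80% power; 58 per group; 20% loss; total raised to 273.

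**The plan's own figure.** Two independent proportions, 83% v 60%: 57 per group (unpooled variance), 58.2 (arcsine) and 60 (pooled). The stated 58 is reproduced.

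**Number analysed.** 273 / 3 = 91 per arm; 91 × 0.80 = 72.8, taken as 73.

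**Assumptions, not in the article.** Attendance share q; gap g, the number of points by which would-be attenders lie below non-attenders on the outcome. The per-protocol set is taken as attenders in one workshop arm against all controls.

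**Bias with no true effect, visit 2 only.** The overall rate is 83% = q × (attender rate) + (1 − q) × (attender rate + g), so the attender rate is 83% − (1 − q)g. The per-protocol difference is therefore (1 − q)g in favour of the workshops. False-positive rates come from simulation (40,000 trials per setting); the two figures are for the unpooled and pooled z test.

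| q | g (points) | Bias (points) | Per-protocol false positives |
|---|---|---|---|
| 60% | 0 | 0 | 6%, 5% |
| 60% | 10 | 0.4 × 10 = 4 | 8%, 9% |
| 60% | 20 | 0.4 × 20 = 8 | 17%, 19% |
| 60% | 25 | 0.4 × 25 = 10 | 23%, 26% |
| 50% | 20 | 0.5 × 20 = 10 | 21%, 24% |
| 80% | 20 | 0.2 × 20 = 4 | 9%, 9% |

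The pairing of 50% attendance with a 25-point gap lies outside the 4 to 10 points quoted: 0.5 × 25 = 12.5. In every row, intention to treat rejected in about 5% of trials and the complier-average estimate (intention-to-treat difference divided by q) was centred on zero.

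**Change from visit 1 to visit 2.** If g is the same at both visits it cancels: bias about 0, false positives about 5% to 6%. If would-be attenders would have improved by d points more without any workshop, the bias is (1 − q)d. With q = 60% and d = 10 this is 0.4 × 10 = 4 points, with about 7% to 8% false positives depending on the assumed persistence of answers between visits. The complier-average estimate again stays at zero.

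**With a true effect.** Take 23 points among attenders, q = 60%, g = 20, visit 2 only. Per-protocol averages 23 + 8 = 31 points; the complier-average estimate averages 23.

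**Precision and power.** With no effect, the intention-to-treat SE is √(2 × 0.83 × 0.17 / 73) = 0.062. Dividing by 0.6 gives 0.104, and the simulated value is 0.105. The per-protocol SE in the same setting with g = 20 is √(0.75 × 0.25 / 43.8 + 0.83 × 0.17 / 73) = 0.079. Intention-to-treat power for 23 points among attenders (g = 0) is about 88% at full attendance, 50% at q = 60% and 38% at q = 50%.

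**The case against.** The strongest reply is that the article does not define the per-protocol set. The definition may lie in a full protocol or analysis plan that is not shown, and its absence here is no fault. A reader might infer that the plan compares all attenders with all controls. The text does not say so, and controls could be excluded for other deviations. That stands. What remains is that the article does choose per-protocol as its method for non-adherence, and no definition based on workshops can be mirrored in the control group.

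Second, the main outcome is to be compared between visits 1 and 2, and a gap already present at visit 1 drops out of a comparison of change. That stands too: the 8% to 26% applies only to an unadjusted visit-2 comparison. Change does not remove differential improvement.

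Third, the quoted remarks prove less than they suggest. A reader might infer from Table 2 that few randomised women attended. The remark explains why social support was not applicable, and sessions were planned for 10 people including companions, so it may mean only that sessions were small. A reader might infer from the Discussion that attenders were better educated. That sentence is about entering a cohort, which affects all arms alike. Neither remark establishes low attendance or a bias in favour of the workshops.

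Fourth, the complier-average estimate has weaknesses of its own. Its test is in essence the intention-to-treat test, so it brings back no power. Attendance at one or more workshops counts women who missed the nutrition session, the one closest to the main outcome. It also assumes that being offered workshops without attending has no effect, which is open to doubt with open-label self-report. These points stand as costs; none of them restores randomisation to the per-protocol comparison.

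**Conclusion.** The concern holds as a flaw in a supplementary analysis. The stated method for non-adherence gives up the randomised comparison in a design where non-attendance is one-sided.

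The size is conditional. With no true effect, 73 per arm and the assumed settings of 50% to 60% attendance and 10 to 25 points between attenders and non-attenders, an unadjusted visit-2 comparison is off by 4 to 10 points, with about 8% to 26% false positives. For change between visits, a stable gap does no harm; a 10-point greater natural improvement in attenders gives 4 points and about 8%. If attenders do not differ, there is no bias.

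A reader might go further and conclude that the trial's main result is compromised, or that the per-protocol result must favour the workshops. The documents support neither: intention to treat comes first and is unaffected, and no attendance rate or attender difference is reported.

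**What to change.** 1. Keep intention to treat as the main analysis.
2. Report attendance by arm, including the number of workshops attended.
3. Add a complier-average estimate on the risk-difference scale for each workshop arm against control, by two-stage regression. Use randomised arm as the instrument and attendance at one or more workshops as treatment received, and adjust for visit-1 consumption. Because controls have no access before the study ends, the unadjusted form is the intention-to-treat difference divided by the proportion attending. The one-or-more definition is where the no-effect-without-attendance assumption is most credible.
4. Keep the per-protocol analysis only as descriptive, and say that it is not a randomised comparison.

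The cost is a change of wording and one extra model on attendance and outcome data. The article says the data had not yet been analysed, so this could be settled before results were known. The downsides are a wider interval (SE about 0.105 against about 0.08 for per-protocol at 60% attendance with no effect), the assumption about women who are offered workshops but attend none, and no recovery of the power lost to non-attendance.

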#### Main outcome

Percentage of participants who reported consuming manufactured or industrial food determined through a sociodemographic and consumption questionnaire (Q1) developed by our research team [48] and administered at t0, t + 2 months and t + 14 months.

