### Sample size

According to the results of the EDDS (Endocrine Disruptors Deux-Sèvres) cohort study, 83% of French women consumed canned food [48]. Thus, we calculated the number of participants based on the primary outcome measure (consumption measure) using a two-sided paired sample *t* test with 0.05 level of significance two-way design and *β* = 0.20. Our hypothesis was that the contextualized intervention would decrease this percentage to 60%, representing a decrease of 23 points, and 58 participants were required for each group. We expected 20% of lost to follow-up participants; consequently, 70 participants are required for each group, out of a total of 210 pregnant women to be included in our study. This number was increased to 273 persons due to significant colostrum loss in an amendment submitted to the Committee for Personal Protection who approved the first protocol (protocol version 10 approved by the Committee for Personal Protection on 15 June 2018).

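### The only comparison written for the main outcome is home visit 1 against home visit 2; no between-arm contrast is stated, and the sample size cites a paired t test

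*Protocol article*

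**What the plan says.** The Study design section describes a "randomized (1:1:1) controlled superiority trial, parallel-designed, three-armed" study. The Main outcome section defines a yes/no measure, the percentage reporting manufactured or industrial food, asked at t0, 2 months and 14 months.

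For the analysis, the Data collection, management, and analysis section says: "Main outcome will be compared between home visit 1 and home visit 2". That sentence names no arm and no test. The next sentence extends the remaining analyses to all three home visits. Comparisons across arms are written in two places only: for baseline measurements, and for the psychosocial questionnaire by ANOVA. Intention-to-treat and per-protocol analyses are planned without a contrast. A logistic regression is planned to look for factors that influence the outcomes; arm is not named as a term.

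The Sample size section says that the number was "based on the primary outcome measure (consumption measure) using a two-sided paired sample" t test, at two-sided 0.05 with β of 0.20. It starts from a cohort in which "83% of French women consumed canned food" and assumes a fall to 60% under the contextualized intervention. This gives 58 per group. No control-arm rate after baseline is given.

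**The concern.** In a parallel superiority trial the effect of the workshops is the difference between arms after the intervention. A change from visit 1 to visit 2 within an arm adds to that effect everything else that happens over two months. The article itself gives reasons to expect such change without workshops:

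- All groups, including control, receive the leaflet at the first home visit (Participants and interventions).
- Table 2 lists the repeated questionnaire as a behaviour change technique, and Table 5 shows that every arm answers it.
- The outcome is self-reported, the trial is open-label, and pregnancy advances in all arms.

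If the sentence is followed as written, a significant fall in group 3 could be reported as efficacy although control fell by as much. Finding significance in one arm and not in another would not repair this, because it does not test the difference between arms.

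**Working it through.** **1. Reproduce the 58 (Sample size section).** Inputs: p1 = 0.83, p2 = 0.60, difference 0.23, two-sided 0.05, power 0.80, so (1.960 + 0.842)² = 7.849.

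Two independent proportions:
- Unpooled: 7.849 × (0.83×0.17 + 0.60×0.40) / 0.23² = 7.849 × 0.3811 / 0.0529 = 56.5, so 57.
- Arcsine: h = 2·asin√0.83 − 2·asin√0.60 = 0.5195; 2 × 7.849 / h² = 58.2.
- Pooled: [1.960·√(2×0.715×0.285) + 0.842·√0.3811]² / 0.0529 = 59.3.

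Paired test: this needs the correlation ρ between a woman's two answers, which the article does not give. With discordant proportion s = p1 + p2 − 2·p11 and p11 = p1·p2 + ρ·√(p1(1−p1)p2(1−p2)), McNemar n = [1.960·√s + 0.842·√(s − 0.23²)]² / 0.23². Paired t n = 7.849·(s − 0.23²)/0.23² + 1.960²/2.

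| ρ (assumed) | s | McNemar n | Paired t n |
|---|---|---|---|
| 0 | 0.434 | 62.0 | 58.5 |
| 0.1 | 0.397 | 56.5 | 53.0 |
| 0.3 | 0.324 | 45.6 | 42.1 |
| 0.5 | 0.250 | 34.6 | 31.2 |

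So 58 fits two independent groups. It fits a paired test only if a woman's two answers are almost uncorrelated.

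**2. How often a before-after test is significant with no workshop effect.** Assumptions, none of them in the article: every arm falls by the same amount f; a proportion c = 3% to 6% switches from no to yes, so c + f switches from yes to no; n is 58 (the stated requirement) to 73 (273/3 = 91, and 91 × 0.8 = 72.8). The number of discordant women m is binomial(n, 2c + f). Given m, the number switching from yes to no is binomial(m, (c + f)/(2c + f)). The rejection probabilities are summed over all outcomes. The lowest value comes from n = 58 with c = 6%, the highest from n = 73 with c = 3%.

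| Equal fall in every arm | Uncorrected McNemar | Exact McNemar | Nominal |
|---|---|---|---|
| 5 points | 13-23% | 8-14% | 5% |
| 10 points | 36-58% | 27-48% | 5% |
| 15 points | 62-85% | 53-79% | 5% |

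The true between-arm difference is zero in every row.

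**3. Power of the between-arm test at home visit 2.** With group 3 at 60%, control at pc and p̄ their mean, power = Φ{[(pc − 0.60)·√n − 1.960·√(2p̄(1 − p̄))] / √(pc(1 − pc) + 0.24)}. For pc = 0.83 and n = 58: (1.752 − 1.251)/0.617 = 0.81, giving 79%.

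| Control at visit 2 (assumed) | n = 58 per arm | n = 72 per arm |
|---|---|---|
| 83% | 79% | 87% |
| 78% | 56% | 65% |
| 73% | 32% | 38% |

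The 72 are the evaluable women per arm if the amended 273 are enrolled and 20% are lost.

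**The case against.** The visit 1 and visit 2 sentence can be read with the one after it as setting time windows: two visits for the main outcome, three for the rest. On that reading the arm comparison is taken for granted. Intention-to-treat and per-protocol analyses presuppose allocated groups, and arm would be a natural term in the logistic regression. The same section also names paired t tests for baseline measurements of three independent arms, so the authors use the word paired loosely. The 58 points the same way. And an article condenses a fuller protocol.

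Much of this stands as evidence of intent. A reader might infer that the sponsor has chosen to set randomisation aside, or that the sample-size text confirms a within-woman test. The document supports neither: no passage says that within-arm tests will be run and read as efficacy, and the paired label is probably an error.

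What does not stand is the idea that the text already contains the right comparison. Intention to treat names a population, not a contrast; arm is not named in the regression; and the across-arm comparisons that are written concern baseline and the psychosocial questionnaire. Nor is this merely detail left to a fuller document: the article does state a comparison and a sizing test, and neither matches the declared design.

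**Conclusion.** The point holds for the plan as written. The stated comparison of the main outcome is before-after, the cited sizing test is paired, and no between-arm contrast is given. Followed literally, the rule does not control the error rate for a workshop effect. The inflation depends on the assumed common fall, the assumed reverse switching and the version of McNemar's test, but both versions exceed 5% in every setting examined. Confidence is high on the missing contrast and lower on what the authors intend.

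A reader might also infer that, once the test is renamed, 58 per group is secure. It is not. That number gives about 79% power only if control stays at 83%, and the leaflet and repeated questionnaire are reasons to expect that it may not.

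**What to change.** In Data collection, management, and analysis, replace the sentence on the main outcome with wording such as: The main outcome at home visit 2 will be compared between randomised arms by intention to treat, group 3 against group 1 first, in a logistic model with arm and the home visit 1 answer. The standardised risk difference with its 95% confidence interval will be reported. Changes from visit 1 to visit 2 within arms are descriptive. The standardisation has to be named, because a logistic model does not itself yield a risk difference.

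In Sample size, replace the paired t test with a two-sided test of two independent proportions, state the control rate assumed at home visit 2, and give power over a plausible range, as in the table above.

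The cost is wording plus a short recalculation. The article says that the data were not yet analysed, so the comparison can be fixed before results are seen. Recruitment is described as complete, so if control is expected to fall, the lower power should be stated openly.
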